##### Simulation study: prospecting the findings for the reality of the national health system

After collecting the effects of implementing the technology-assisted primary care strategy, we will simulate a situation adapted to the scenario of interest,  the national public health system, the SUS (Fig. 2). This strategy has been used to provide subsidies (measurements) related to changes safely and efficiently before they are implemented on a large scale [28].

e will use simulations considering the characteristics of the basic health units that provide primary dental care for children. We will create a specific model considering the distribution of variables in the sample for outcomes collected in trials but prospecting for a wider population eligible for primary care in SUS. We will use some index variables, e.g. caries experience, that we have collected in the trials and a similar one can also be found in official national data. The relationship between such variables and the studied outcomes will be investigated in our sample and will guide the model building.

Finally, using a bootstrap technique, we will simulate data equivalent to SUS reality, considering appropriate variables as reference for that, as mentioned. We will collect updated official data on the impact of the pandemic on the Brazilian public health system and data on oral health conditions in the age group obtained through the last oral health survey (SB Brasil 2010) [29]. We will assume the essential characteristics of these units, which will also be considered in this simulation model. Some scenarios will be set to represent different contexts from different Brazilian regions.

From this simulation study, we hope to find the mean values and their 95% confidence intervals related to the problem-solving rate, reduction of waiting for time and user satisfaction related to the implementation of technology-mediated health care in the primary care of children assisted by the SUS.

##### Economic and social impact assessment

Some economic evaluations were outlined to answer the efficiency of resource allocation when implementing teleassistance activities to solve the pent-up demand caused by the pandemic. To comprehend a broader overview of the economic impact of this implementation process, we will consider the different effects explored in the trials, both child- and parent-centred.

(a) Perspective and Time Horizon: We will adopt a societal perspective for the analyses. The time horizon will be set as the trans-pandemic time, being limited by the beginning of social distancing in Brazil and the date of return to normality of activities officially determined for it according to official government recommendations, as end of the period of interest. Eventually, subgroup analyses will be considered for different Brazilian regions with different profiles regarding the duration of the pandemic. Alternatively, we may also model data using another time horizon, in which we consider the achievement of an ideal vaccination rate in Brazil (or in specific regions).

(b) Type of Evaluation/Effects: Three different trial-based economic evaluations will then be performed using cost-effectiveness approaches. A different effect will be used for each one (Fig. 6). Mainly, data will be extracted from trials described elsewhere in this protocol. Modelling strategies will be used to simulate more prolonged effects than those measured in the trials.

**Fig. 6 Fig6:**
[figure not shown]
Economic evaluations (cost-effectiveness type), respective effects, questions to be answered and possible subgroup analyses foreseen

(c) Costs: The costs will be considered as described below for each assessment. The unit of analysis will be the research participant (patient/child) to which primary care was being directed and the strategy of micro-costing. Resources used will be valued as described in the Fig. 7. The direct costs will be those related to the provision and installation of services. Indirect costs will consider the patient's cost for the use of dental services or costs derived from care) that must be computed in a broader character (Fig. 5). All costs will be valued in Brazilian Real and converted into dollars.

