#### Outcomes

As the primary outcome for this before-and-after study, we consider problem-solving, considering the participant as the measurement unit. We will consider all the complaints pointed out by patients and their families during the baseline consultation. To measure that, a 2-weeks-later interview using the same platform (V4H) will address aspects relevant to understanding if the patients' and families' demands are solved during this time. A checklist to identify possible barriers and facilitators related to each type of complaint will be employed on these interviews. The time to resolution of the complaint will be computed as a secondary outcome.

Children will also be asked to toothbrush and floss during this assessment consultation. An external assessor will check the problem-solving related to the demand for oral hygiene orientations. The guidelines for orientation will be used as the reference standard to check if the demand was solved. If the child fulfils all oriented aspects, the demand is fully solved. If at least one assessment criterion is fulfilled, it is considered a partially solved demand. Cases of non-compliance with intervention sessions or those families that give up the consultations were also considered to understand the studied service's implementation.

Other outcomes will be assessed as secondary ones. The teleservice platform will measure consultation time. Technological and non-technological difficulties during the consultation (absences or delays, non-compliance, difficulties in using the platform, accessing the internet or even the computer or mobile phone) will be registered by an external assessor in a specific file at the end of the online session. The caregivers' and child's perceptions on the use of technologies in primary dental care will be collected by specific questionnaire [21] in the two-week-later assessment.

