#### Sample size and recruitment

As we have a demand study, all children enrolled for dental treatment at the dental unit will be potentially recruited for this before-and-after study and no sample size is required. The child will be our unit of analysis for that. As previously described, refusals and non-compliance with non-face-to-face consultations will also be registered as outcomes. At least five attempts to contact participants who accept to participate will be used. In these attempts, we will consider different manners of communication, including phone calls, text and Whatsapp messages, email messages (when possible).

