#### Interventions

The family (including all children enrolled at the unit from the same family) will be randomized using stratified randomization by one researcher to one of the groups (intervention vs waiting list). The stratification will be performed considering the dentist will provide the non-face-to-face consultation and the week for inclusion. In this way, balanced randomization was obtained per professional each week.

Randomization order will be generated by the website sealedenvelope.com. The list will be stored under the supervision of the person responsible for randomization ([name]) and the principal investigator ([name]), in cloud storage and on a USB stick. The dentist who will provide the dental care will be unaware of randomization. They will receive the list with families/patients they are supposed to care for each week sent via email by the person in charge of randomization.

The two groups will differ according to the time of application of the intervention and outcome assessment. The non-face-to-face intervention group will receive the intervention immediately after randomization (t0). Then, after two weeks, the outcome will be measured as described further (t2). The waiting list group (control) will not receive the intervention at this time  and then assessed after the same period to permit controlling the answers (t2). Once this is done, the children on the waiting list will receive the intervention regularly (t3) and become part of the previously detailed list of before-and-after study participants. However, for the present RCT, only data without intervention will be considered (t2). The intervention will be provided as described in the before-and-after study *Interventions* section. Both groups will have been contacted by a research team member to explain the study and will have answered a baseline questionnaire previous to randomization (t-2). At this time, all participants will know the teleservice will be available, but they will not know when that will happen.

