#### Outcomes

We set the family's perception of dental care quality as the  primary outcome. We will consider the caregiver's perspective (those who participate in the non-face-to-face consultation) measured two weeks after the intervention (teleservice test group) or two weeks after waiting for care (control group) (Figs. 2, 3). The SERVQUAL questionnaire will be used [24] (Additional file 3). SERVQUAL is a summary instrument of multiple scales, with a high level of reliability and validity already used in Portuguese [24]. It can be used to understand users' expectations and perceptions concerning a wide range of services. In the present study, it is supposed the participants evaluate the degree to which they perceived the proposed service.

The questionnaire consists of 22 items, divided into 5 dimensions related to the service (tangible aspects—appearance of physical facilities, equipment, personnel and communication materials; reliability—ability to perform the promised service safely and correctly; responsiveness—willingness to help clients and provide prompt service; assurance—knowledge and courtesy of employees and their ability to inspire trust and empathy—personalized attention given to customers) [25]. A total of 100 points is allocated among the five dimensions.

As secondary outcomes, we define the gap between users' perception and expectations, each partial assessment for five different domains included in the SERVQUAL questionnaire, and finally, the overall participants' perception of the service.

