##### Before-and-after study

Firstly, we will calculate the problem-solving rate achieved with non-face-to-face care. Besides, a subgroup analysis will consider different demands identified. We will also calculate the average time of resolution of the demands (difference between the moment of the appearance of the complaint or demand and the moment of its resolution) and the reduction of the waiting time (time-lapse from when the care is provided and the regular face-to-face activities re-opening).

Regarding children's and caregivers' perception, we will calculate the usability rate (ease of use reported by caregiver users), satisfaction with the tools, behavior towards proposed strategies, and difficulties encountered, dividing them into difficulties with technologies and not related to technologies. Regression models will demonstrate the association of demand solving and the independent variables mentioned above. The same statistical approach will be used to outcomes related to the children's and caregivers' perception (usability, satisfaction, and behaviour to the technologies with the resolution of cases) and the time to resolution of complaints will be considered a dependent variable of conditional risk models. The events will be attention needs and the time counted from the last face-to-face contact. In these models, we will explore as independent variables the other variables also mentioned above, as well as aspects related to the difficulties reported by users.

The qualitative content analysis of the non-face-to-face consultations mediated by technology will be descriptive. It will look for possible explanations to different caregivers' perceptions and identify barriers and facilitators associated with the type of care offered.

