(e) Analysis Plan: The cost-effectiveness strategy will be used for economic analyses. Incremental values will be calculated both for costs and effects. Therefore, the difference between the new strategy and the one you want to replace will be calculated. (ΔE = E_with_tele_ – E_without_tele_ and ΔC = C_with_tele_ – C_without_tele._ The confidence intervals will be estimated, for each parameter, using the bootstrap technique and considering the sample values referring to costs, effects, incremental costs and incremental cost ratio incremental effectiveness.

The decision-making will depend on the interpretation that will be made of the values collected in the cost-effectiveness plane. Depending on the quadrant in which these simulation results are placed, it may be called dominant or dominated, so an incremental-effectiveness cost ratio calculation may be required for the decision to be made. If the results are in the Northeast or Southwest quadrant (Fig. 8), the incremental cost-effectiveness ratio will help to decide whether or not the intervention will be cost-effective, that is, whether the extra expenditure attributed to the strategy is really worth the effect achieved by it, or even, whether what will be saved with the new strategy is worth the loss that has in its effect.

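### The child is the stated unit of analysis in the before-and-after study and the economic evaluations, but the planned regressions and bootstraps make no provision for siblings clustered in families

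*Protocol article*

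**What the plan says.** The protocol article uses two units.

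- **Allocation (RCT, Interventions):** "The family (including all children enrolled at the unit from the same family) will be randomized using stratified randomization". Siblings therefore always share an arm.
- **RCT primary outcome and sample size (RCT, Outcomes; Sample size and recruitment):** SERVQUAL is answered from the caregiver's perspective, and the calculation counts family representatives (306) and families (368).
- **Before-and-after study (Outcomes; Sample size and recruitment):** for the primary outcome, "we consider problem-solving, considering the participant as the measurement unit". For the study as a whole, "The child will be our unit of analysis for that".
- **Economic evaluations (Economic and social impact assessment, (c) Costs):** "The unit of analysis will be the research participant (patient/child) to which primary care was being directed". The opening paragraph of that section says the effects used will be both child-centred and parent-centred.

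Two analysis statements follow. Under Statistical methods, Before-and-after study: "Regression models will demonstrate the association of demand solving and the independent variables mentioned above". Under (e) Analysis Plan of the economic section: "The confidence intervals will be estimated, for each parameter, using the bootstrap technique". Neither mentions siblings, within-family correlation or the unit to be resampled, and nor does the rest of the article.

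**The concern.** Siblings share a home, a caregiver and internet access, so their outcomes and costs are plausibly alike. A regression or bootstrap that takes each child as a separate draw then credits the data with more information than they hold.

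The quantities exposed are the problem-solving rate, its association with family-level covariates (for example caregiver education or socioeconomic factors), incremental costs and effects, and what is built on them: the acceptability curves, the probabilistic sensitivity analyses and the expected value of perfect information. The simulation study projects trial relationships to the national health system with 95% confidence intervals, so understated uncertainty could carry into the policy-facing estimates.

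There is a second, smaller question. A child-level unit combined with a parent-centred effect leaves open how a family with two or three enrolled children contributes its one caregiver score.

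**Working it through.** **1. The plan's own figure.** Inputs from the RCT section, Sample size and recruitment: difference 0.17, SD 0.53. Assumed, because not stated: two-sided 5%, 80% power, 1:1 allocation.

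n per arm = 2 × (1.960 + 0.842)² × (0.53/0.17)² = 152.6, rounded up to 153, so 306 in total. This matches the plan. Adding 20% gives 153 × 1.2 = 183.6, rounded up to 184 per arm, so 368. This matches too. Both figures count families or their representatives, so sibling clustering does not enter the RCT sample size.

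**2. Bound on family size.** The Study setting section gives 750 enrolled children. If they come from at least the 368 families to be randomised, mean family size is at most 750/368 = 2.04. The documents give no family count, so 1.25 to 2.04 is an assumed range.

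**3. Design effect.** For a mean, a rate, or a contrast between whole families, with equal family size m and intra-family correlation ρ (assumed 0.1 to 0.6): DEFF = 1 + (m − 1)ρ. The correct interval is √DEFF times as wide as the child-level one. A nominal 95% child-level interval covers 2Φ(1.96/√DEFF) − 1.

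| m | ρ | DEFF | Width ratio | Coverage of child-level CI |
|---|---|---|---|---|
| 1.25 | 0.1 | 1.025 | 1.01 | 94.7% |
| 1.25 | 0.3 | 1.075 | 1.04 | 94.1% |
| 1.25 | 0.6 | 1.150 | 1.07 | 93.2% |
| 1.5 | 0.3 | 1.150 | 1.07 | 93.2% |
| 1.5 | 0.6 | 1.300 | 1.14 | 91.4% |
| 2.04 | 0.1 | 1.104 | 1.05 | 93.8% |
| 2.04 | 0.3 | 1.311 | 1.14 | 91.3% |
| 2.04 | 0.6 | 1.623 | 1.27 | 87.6% |

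At ρ = 0 or m = 1, DEFF is 1 and nothing changes. Uneven family sizes raise the figure: DEFF = 1 + ((1 + CV²)m − 1)ρ. With CV 0.5, m = 2.04 and ρ = 0.5 this is 1.77, so 33% wider.

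**4. Bootstrap check by simulation.** Settings: two arms, 368 families randomised as units, assumed sizes 1 to 4 with mean about 2.05, a continuous child outcome, no true difference, 600 runs per row.

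| ρ | True SE | Child-level bootstrap SE | Coverage, child resampling | Coverage, family resampling |
|---|---|---|---|---|
| 0 | 0.074 | 0.074 | 95% | 95% |
| 0.1 | 0.079 | 0.072 | 93% | 95% |
| 0.3 | 0.086 | 0.073 | 92% | 95% |
| 0.5 | 0.096 | 0.072 | 85% | 95% |

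Resampling families restores nominal coverage. Resampling children does not, unless the correlation is zero or small.

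**The case against.** The strongest reply is that the article nowhere says siblings will be treated as independent. A child unit of analysis is compatible with GEE, clustered standard errors or a family bootstrap, and an analysis plan or health-economics plan that is not shown may specify them. That stands as a limit on the wording: independence would be an inference from silence. It does not remove the point, because the article itself fixes an analysis unit different from its allocation unit and describes the regressions and bootstraps on that unit without reconciling the two.

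Other parts of the reply also stand:

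- **No family size or correlation is given.** The size of the effect is assumed throughout. For covariates that vary within a family, such as a child's own caries experience, ignoring clustering can overstate the standard error instead.
- **Randomisation is not the issue in the before-and-after study.** It is a single-group comparison in which only natural sibling clustering matters.
- **Problem-solving is not wholly a caregiver report.** For the oral hygiene demand, an external assessor checks the child directly.

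A reader might go further and infer that one SERVQUAL score will be copied to every sibling. With assumed family sizes of 1, 2 and 3 in proportions 0.4, 0.4 and 0.2, a child-level test on copied scores would have a design effect of 3.8/1.8 = 2.11 and a type I error near 17.7%. No passage plans such a test. The RCT is sized in families, the costing-unit sentence sits under Costs, and the figure listing the effects is not shown. Likewise, nothing says siblings share a session, so double counting of caregiver time or internet cost is a risk to close and not a demonstrated error.

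**Conclusion.** The point holds in a limited form. The stated unit of analysis conflicts with the family structure that the protocol recognises when it randomises, and the regressions and bootstraps are described without provision for it. If they are run at child level as stated and siblings are positively correlated, intervals for overall rates, family-level associations and incremental costs and effects will be too narrow.

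Under the assumptions in steps 2 and 3, the shortfall runs from negligible to a correct interval about 27% wider with equal family sizes, and somewhat more if sizes are uneven. The documents do not support saying that the intervals are too narrow as a matter of fact, nor that the RCT is compromised: its primary comparison and its 306/368 are family-level. This deserves correction before analysis, since the simulation study and the economic results build on these intervals.

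**What to change.** - **Statistical methods, Before-and-after study:** state that child-level models, including the time-to-resolution models, use GEE, a family random effect or family-clustered standard errors, and that the interval for the problem-solving rate is family-clustered.
- **Economic section, (e) Analysis Plan and (f) Sensitivity analyses:** state that bootstrap and probabilistic draws are based on whole families. Resample within arm only for the randomised contrast. For the single-group before-and-after data, resample families without regard to arm.
- **Economic section, (b) and (c):** state that any caregiver-level (parent-centred) effect enters once per family and that, if siblings share a session, its costs are counted once or split across them.
- **Reporting:** give the number of families, the distribution of children per family and the estimated intra-family correlation.

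The cost is a few lines of text and code plus a family identifier, which the randomisation already requires for the randomised families. Intervals become somewhat wider. No new data are needed, and the RCT sample size and primary comparison do not change.

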**Fig. 7 Fig7:**
[figure not shown]
Cost components to be valued for the economic evaluations

Direct costs will be computed considering the time of use of the teleservice. This time will be recorded on the platform and by the service professional to double-check. For the calculation for the professional cost: the salaries of professionals will be based on the official national data will be used. With this, it will be multiplied by the time spent. Sensitivity analyses will be performed using data from different regions and/or different available services/positions.

The costs for the installation and maintenance of the teledentistry system take into account the program's implementation and its continuous operation. This type of cost will consider the time spent by the team for developing the system and the cost of maintaining and using the platform. An hourly value for using the technology will be calculated based on system capacity and usage flow data per month [30] and thus the value of the time obtained. A similar strategy will be made considering the expenses related to training and training of the team to implement the strategy [31].

To value the cost of using the technology by the patient/family, the average prices for 1Mbps of internet and Kwh of energy in Brazil, taking into account the time spent in each consultation. The value for patient's and caregiver's time and caregiver will be valued using arbitrary reference values (for example, the minimum wage and/or average salary of the population) and the time spent during care.

To value the treatments received outside the dental unit, the average value per procedure was obtained from a data repository of costs related to care provided at the same unit when performing another clinical study (NCT02473107). If a child needs to perform a restoration during the period, a value is estimated based on that repository.

In the case of unresolved complaints or patients who miss the expected follow-up until the end of the pandemic, the costs of possible complications will be valued based on the expected outcomes using models.

In the case of patients who will not receive the intervention, the costs of the intervention will not be considered since face-to-face care at the time of the pandemic is suspended (Fig. 5).

(e) Analysis Plan: The cost-effectiveness strategy will be used for economic analyses. Incremental values will be calculated both for costs and effects. Therefore, the difference between the new strategy and the one you want to replace will be calculated. (ΔE = E_with_tele_ – E_without_tele_ and ΔC = C_with_tele_ – C_without_tele._ The confidence intervals will be estimated, for each parameter, using the bootstrap technique and considering the sample values referring to costs, effects, incremental costs and incremental cost ratio incremental effectiveness.

The decision-making will depend on the interpretation that will be made of the values collected in the cost-effectiveness plane. Depending on the quadrant in which these simulation results are placed, it may be called dominant or dominated, so an incremental-effectiveness cost ratio calculation may be required for the decision to be made. If the results are in the Northeast or Southwest quadrant (Fig. 8), the incremental cost-effectiveness ratio will help to decide whether or not the intervention will be cost-effective, that is, whether the extra expenditure attributed to the strategy is really worth the effect achieved by it, or even, whether what will be saved with the new strategy is worth the loss that has in its effect.

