**Fig. 5 Fig5:**
[figure not shown]
Clinical decision-making protocol to meet the patients’ and families’ reported demands related to oral care

An electronic form was created to guide consultation and permit data collection. The data collected by the form was stored under the supervision of the principal investigator ([name]), in cloud storage and on a USB stick.

The teleservice will be carried out through a digital platform (Video for Health—V4H). This platform is innovative, 100% Brazilian, created by the Research and Extension Center (Lavid) of the Informatics Center in Federal University of Paraiba (UFPB) in partnership with the Federal University of São Paulo (Unifesp) and financially supported by the National Network of Teaching and Research (RNP). The Teledentistry Center of Dental School, University of São Paulo contributed to adapting platform functionalities to the context of the SUS and the private sector in Brazil. The platform offers confidentiality in data traffic between participants, preservation for the time it is necessary to recover recorded videos, secure recording (with encryption) and registration in blockchain or trust protocol and a distributed registration technology to guarantee security in using it.

The operators were trained to use the V4H platform resources by expert researchers in teleservice and V4H development and support staff. Besides, they will receive the necessary technical support from the V4H team during the study. They are also calibrated on following Standard Operational Procedures to guide the consultation in a standardized way. Families enrolled in the Teletrailer program will receive information and support to use the platform from the Teletrailer team.

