#### Independent variables collection

For both clinical trials described, available data will be collected from a data repository (dental records) administered by the researchers. Variables as time since the last consultation, oral health conditions associated (previous needs, caries experience, treatment adhesion/retention, oral-related habits, socioeconomic factors) may be used as independent variables. In addition, other independent variables will be collected parallel to intervention (teleconsultation), as changes in habits during the pandemic, level of education, age and occupation of the caregiver users involved in teleservice and previous experiences in health assisted by technologies.

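### Costed teleservice time is not separated from research time, so incremental cost is liable to be overstated by an unknown amount

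*Protocol article*

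**What the plan says.** All references are to the protocol article.

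- **Consultation time.** In the Outcomes of the before-and-after study it is a secondary outcome: "The teleservice platform will measure consultation time".
- **Time as the cost driver.** Under Economic and social impact assessment, (c) Costs: "Direct costs will be computed considering the time of use of the teleservice. This time will be recorded on the platform". The second of these sentences reads in full: "This time will be recorded on the platform and by the service professional to double-check". Professional cost starts from official salary data: "With this, it will be multiplied by the time spent". For the platform, "An hourly value for using the technology will be calculated based on system capacity and usage flow data per month". Family internet and energy are valued on the time of each consultation. Patient and caregiver time is valued on the time that care takes.
- **Research content.** The Interventions section of the before-and-after study says: "An electronic form was created to guide consultation and permit data collection". Independent variables collection says that "other independent variables will be collected parallel to intervention (teleconsultation"), and lists habit changes, the caregiver's education, age and occupation, and earlier experience of technology-assisted health care. The Outcomes section adds a semi-structured interview without saying when it takes place, and holds the two-week outcome interview on the same platform.
- **Comparator.** Patients who do not receive the intervention carry no intervention cost ((c) Costs). Incremental cost is the with-teleservice cost minus the without-teleservice cost ((e) Analysis Plan).

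**The concern.** A cost-effectiveness analysis meant to inform the public health system should charge the intervention with the time that care takes. Time spent asking questions for a regression model or a qualitative study would not recur in routine use. If those questions are asked while the session clock runs, their minutes are paid for at the professional's salary, the platform's hourly value and the family's connection cost. The comparator has no such session, so nothing offsets the excess.

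At stake are the incremental cost in three economic evaluations, the position on the cost-effectiveness plane that the article uses for decisions, the cost inputs to the planned budget impact analysis, and consultation time as a reported outcome. Once only session totals are stored, an analyst cannot remove the excess without going back to the recordings.

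**Working it through.** The article gives no session length, research minutes, unit cost or cost-effectiveness ratio, so there is no stated figure to reproduce. The check has three parts.

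**1. Do research minutes probably fall inside the recorded time?**

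- Habit changes stand in the same list as caregiver education, age, occupation and technology experience (Independent variables collection). The three-part consultation in the Interventions section places habit changes inside the call. That suggests the rest of the list is gathered there too.
- Education, age, occupation and technology experience are not among the stated contents of the three parts.
- Families who decline research may still have the teleconsultation, but without the research data collection (eligibility criteria, before-and-after study). The article thus treats research collection as an addition that can be separated from care.
- The qualitative content analysis is applied to the consultations themselves (Statistical methods, before-and-after study).

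This makes it probable but not certain.

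**2. Does anything in the article take those minutes out?**

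- The professional's record is a second clock on the same duration. It confirms the total and is not said to split it.
- The sensitivity analysis of professional cost changes the region, service or position, not the minutes.
- The deterministic analyses use the confidence limits of effects and costs, and the probabilistic analyses use the sampled distributions ((f) Sensitivity analyses). A systematic excess is present in every sampled session, so it shifts the estimate and its limits together.

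**3. How large could the effect be?**

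Define:
- f = research share of recorded time (assumed);
- s = share of recorded incremental cost ΔC that scales with that time (assumed);
- ΔE = incremental effect, taken as unchanged and positive, with ΔC positive.

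Removing research minutes lowers the time-driven part, s·ΔC, by the fraction f. So:

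care-only ΔC = ΔC − f·s·ΔC = ΔC·(1 − f·s)

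reported ratio / care-only ratio = 1/(1 − f·s)

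For f = 0.10 and s = 0.25: 1/(1 − 0.025) = 1.026. For f = 0.10 and s = 1: 1/0.90 = 1.111.

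Overstatement of cost per effect, in percent:

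| f | s = 0.25 | s = 0.50 | s = 0.75 | s = 1.00 |
|---|---|---|---|---|
| 0% | 0 | 0 | 0 | 0 |
| 5% | 1.3 | 2.6 | 3.9 | 5.3 |
| 10% | 2.6 | 5.3 | 8.1 | 11.1 |
| 20% | 5.3 | 11.1 | 17.6 | 25.0 |
| 30% | 8.1 | 17.6 | 29.0 | 42.9 |
| 40% | 11.1 | 25.0 | 42.9 | 66.7 |

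The s = 1 column is also the overstatement of consultation time itself, f/(1 − f). If teleservice lowers outside-treatment and complication costs, those savings shrink the net ΔC and s can exceed 1; the relative error is then larger than the table shows.

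**The case against.** The strongest reply is that no sentence in the article says research minutes are costed. Collecting data parallel to the intervention may mean alongside the call and off the clock. (c) Costs defines direct costs as those of providing and installing services, which asking a caregiver's occupation is not. Patient and caregiver time is already worded as time in care. Most of what the electronic form holds (medical history, oral condition, habits, complaints) belongs to the consultation and would exist in routine use. What is left is a few short questions: one minute in a 30-minute session would be 30/29 − 1 = 3.4% of care time. Fig. 4, Fig. 7 and Additional file 2, which may say more, are not shown.

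Most of this stands, and it limits the claim. It does not remove it. The operative costing rule is stated, and it rests on recorded time of use with no care-only qualifier for the professional, platform and connection components. The placement of the semi-structured interview is open, and it could take more than a minute. Read literally, time of use of the teleservice could also take in the two-week interview, which runs on the same platform.

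A reader might infer more: that research time is in fact charged to the intervention, that cost per effect is therefore overstated in all three evaluations, and that the ratio moves by nearly the same share as the minutes. The article does not support this. Research minutes in the costed time are an inference. ΔC also contains system development and maintenance, training, treatments received elsewhere and modelled complications, so s need not be near 1. The direction for the ratio needs positive ΔC and ΔE, while (e) Analysis Plan allows for dominance and for results in the Southwest quadrant.

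**Conclusion.** The concern holds in a limited form. Consultation time and most time-based costs rest on total recorded teleservice time, research-only items appear to be collected with the teleconsultation, and no stated step separates the two. Any research minutes push incremental cost in one direction, upwards.

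The size is unknown. Over assumed research shares of 5% to 40% and time-driven cost shares of 25% to 100%, the ratio would be overstated by about 1% to 67%. The upper end needs far more research time than a few short questions would take. A 10% research share gives 2.6% to 11.1%. If the items are asked outside the call, and the two-week interview is not costed, the effect is 0%. These figures illustrate the mechanism and are not estimates for this trial.

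The point touches a secondary outcome and the economic evaluations. It does not touch the primary outcome of either clinical study.

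**What to change.** 1. State in the costing plan that consultation time and all time-based costs mean care-only minutes.
2. Add start and end time stamps in the electronic form around research-only segments (caregiver education, age, occupation, earlier technology-assisted care, and the semi-structured interview if it is held in the call). Alternatively, ask those items of the same caregiver outside the timed session.
3. State that the two-week outcome interview is excluded from costed time.
4. For sessions already held, retime the research segments from the recorded videos, or run a sensitivity analysis on the research share f.

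Moving the items to the baseline questionnaire at t-2 looks simpler but is not sound as it stands. That questionnaire is described only for the randomized trial, whereas the before-and-after study invites every enrolled child. Its respondent may also not be the caregiver who takes part in the call, whose characteristics are the ones wanted.

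The cost is a small change to the form, a few sentences in the costing plan, and some retiming work.
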